## Inclusion Criteria

1. Male and female patients aged 18 to 65 years old at baseline;
2. Subjects who experienced ETV treatment for at least 1 year;
3. Serum HBV DNA≤1000 copies/ml;
4. HBsAg positive;
5.
[figure not shown]

[figure not shown]
ALT >2 ULN but <10 ULN and HBeAg positive before NAs treatment;
6. Negative urine or serum pregnancy test (for women of childbearing potential) documented within the 24-hour period prior to the first dose of test drug;
7. Absence of cirrhosis determined by liver ultrasound;
8. Agree to participate in the study and sign the patient informed consent.

## Exclusion Criteria

1. Patients who had previously developed drug resistance to ETV;
2. Other antiviral, anti-neoplastic or immunomodulatory treatment (including supraphysiologic doses of steroids and radiation) *6 months prior to the first dose of randomized treatment (except for 7 days of acyclovir for herpetic lesions more than 1 month prior to first administration of randomized treatment). Patients who are expected to need systemic antiviral therapy other than that provided by the study at any time during their participation are also excluded;
3. Women with ongoing pregnancy or breast-feeding;
4. Co-infection with active hepatitis A, hepatitis C, hepatitis D (Those hospitals which have the ability to do the test will do) and/or human immunodeficiency virus (HIV);
5. Evidence of decompensated liver disease (Child-Pugh score>5). Child-Pugh>5 means, if one of the following 5 conditions are met, the patient must be excluded:
6. Serum albumin <3.5 g/L;
7. Prothrombin time ≥3 seconds prolonged;
8. Serum bilirubin >34 µmol/L;
9. History of encephalopathy;
10. History of variceal bleeding;
11. Ascites
12. History or other evidence of a medical condition associated with chronic liver disease other than viral hepatitis (e.g., hemochromatosis, autoimmune hepatitis, metabolic liver disease, alcoholic liver disease, toxin exposures, thalassemia);
13.
[figure not shown]
Signs or symptoms of hepatocellular carcinoma, patients with a value of alphafetoprotein >100 ng/mL are excluded, unless stability (less than 10% increase) has been documented over at least the previous 3 months. Patients with alphafetoprotein values >20 ng/mL but
[figure not shown]
 ≤100 ng/mL may be enrolled, if hepatic neoplasia has been excluded by liver imaging;
14. Neutrophil count <1500 cells/mm^3^ or platelet count <90,000 cells/mm^3^ at screening;
15. Hemoglobin <11.5 g/dL for females and <12.5 g/dL for men;
16. Serum creatinine level >1.5 ULN in screening period.
17. Phosphorus <0.65 mmol/L;
18. ANA>1:100;
19. History of severe psychiatric disease, especially depression. Severe psychiatric disease is defined as treatment with an antidepressant medication or a major tranquilizer at therapeutic doses for major depression or psychosis, respectively, for at least 3 months at any previous time or any history of the following: a suicidal attempt hospitalization for psychiatric disease, or a period of disability due to a psychiatric disease;
20. History of a severe seizure disorder or current anticonvulsant use;
21. History of immunologically mediated disease, (e.g., inflammatory bowel disease, idiopathic thrombocytopenic purpura, lupus erythematosus, autoimmune hemolytic anemia, scleroderma, rheumatoid arthritis etc.);
22. History of chronic pulmonary disease associated with functional limitation;
23. History of severe cardiac disease (e.g., NYHA Functional Class III or IV, myocardial infarction within 6 months, ventricular tachyarrhythmias requiring ongoing treatment, unstable angina or other significant cardiovascular diseases);
24. Major organ transplantation or other evidence of severe illness, malignancy, or any other conditions, which would make the patient, in the opinion of the investigator, unsuitable for the study;
25. History of thyroid disease poorly controlled on prescribed medications, elevated thyroid stimulating hormone (TSH) concentrations with elevation of antibodies to thyroid peroxidase and any clinical manifestations of thyroid disease;
26. Evidence of severe retinopathy or clinically relevant ophthalmologic disorder (e.g. due to hypertension or diabetes mellitus, CMV retinitis, macular degeneration);
27. Patients consuming alcohol more than 20g/day for women and 30g/day for men in the 6 months preceding enrollment;
28. Evidence of drug abuse or treatment with methadone within one year of study entry.
29. Patients included in another trial or having been given investigational drugs within 12 weeks prior to screening;
30. Inability or unwillingness to provide informed consent or abide by the requirements of the study.

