| Co-Investigator: | [name], [name], [name], [name], [name], [name] |

SYNOPSIS OF PROTOCOL

| TITLE | Combination therapy of pegylated interferon-alpha-2b, nucleoside/nucleotide analogues (NAs) and GMCSF in NA-experienced chronic hepatitis B patients: A prospective, randomized open-label trial (Anchor study) |
| --- | --- |
| SPONSOR | The Chinese National Thirteenth Five Years Project in Science and Technology (2017ZX10202201) |
| INDICATION | NA-experienced CHB |
| OBJECTIVES | Primary: To compare the efficacy (HBsAg loss) and safety of pegylated interferon alfa-2b therapy plus entecavir (ETV) with or without GMCSF or ETV alone in NA-experienced CHB patients who had sustained HBV DNA suppression by ETV treatment. |
| TIRAL DESIGN | A multi-center, randomized, prospective, open-label Phase IV clinical trial. Patients will be randomized 1:1:1 in the IFN+ETV +GMCSF combination therapy group, IFN+ETV group or ETV group. |
| NUMBER OF PATIENTS | Total N 257 |
| TARGET POPULATION | The subjects who pre-treated by ETV for at least 1 year and achieved HBV DNA ≤10^3^ copies/ml & HBsAg <3000 IU/ml. Patients were excluded if they had previously developed drug resistance to ETV, or received IFN or systemic antiviral therapy within the previous 6 months. Patients were also excluded if they were coinfected with the human immunodeficiency virus, hepatitis C virus or hepatitis D virus or if they had decompensated liver disease (defined as a Child-Pugh Score B or C), pregnancy or lactation, or any other contraindication for IFN therapy |
| LENGTH OF STUDY | 96 weeks treatment  24 weeks follow up |
| DURATION OF STUDY | 42 months after first patient randomized |
| INVESTIGATIONAL PRODUCTS  DOSE/ROUTE/REGIMEN | Group 1: Entecavir 0.5mg once per day; P.O.  Group 2: Entecavir 0.5mg once per day (cessation at week 48); P.O. Pegylated interferon alfa-2b 180ug once per week; S.C.  Group 3: Entecavir 0.5mg once per day (cessation at week 48); P.O. Pegylated interferon alfa-2b 180ug per week; S.C. plus GM-CSF (Teerli, Xiamen Amoytop Biotech Co., Ltd, China) 75 μg once-daily for the first 5 consecutive days each month; S.C. |
| ASSESSMENT OF EFFICACY | Primary Endpoint:  HBsAg loss at Week 96.  Secondary Endpoint:   1. HBsAg seroconversion 2. Proportion of patients who achieve undetectable HBV DNA 3. Quantitative HBsAg measurement 4. HBeAg seroconversion 5. ALT normalization 6. Sustained virologic response at the end of follow-up |

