## Screening examination and eligibility screening form

All legal guardians/subjects must sign and date the most current IRB/IEC-approved written informed consent/assent (where appropriate) before any study-specific assessments or procedures are performed.

The assessments in Table 2 must be obtained within a period of no more than 8 weeks before the subject is randomized, except as noted. Subjects must fulfill all the entry criteria for participation in the study (see Sections 6.2 to 6.3). An Eligibility Screening Form (ESF) documenting the investigator’s assessment of each screened subject with regard to the protocol’s inclusion and exclusion criteria is to be completed by the investigator. A screen failure log must be maintained by the investigator.

Table 2 Screening Assessments

| Medical history and physical examination | Includes family history of HBV, concomitant medication (including for CHB), and vital signs (blood pressure, heart rate, temperature). |
| --- | --- |
| Ophthalmological examination | By ophthalmologist and including fundoscopic examination, visual acuity assessment, visual field testing, and color visual testing. Any subject who develops ocular symptoms should receive a prompt eye examination by an ophthalmologist and additional examinations as necessary. |
| Ultrasound and liver elastography | To rule out hepatocellular carcinoma and liver cirhosis. Further liver imaging assessment may be performed if necessary. |
| Liver biopsy | Optional |
| HCG pregnancy test | For females of childbearing potential, a negative urine or serum HCG test needs to be documented within 24 hours prior to baseline. Note that the test may be performed at the baseline visit, provided that the result is available prior to randomization and commencement of treatment. |
| Hematology | Complete blood count (hemoglobin, hematocrit, total white blood cell [WBC] count, differential WBC count [neutrophils, lymphocytes, monocytes, eosinophils, basophils]), platelet count, international normalized ratio (INR) |
| Clinical chemistry | ALT, AST, GGT, total bilirubin, alkaline phosphatase, total |
|  | protein, albumin, blood urea nitrogen (BUN)/urea, creatininee, uric acid, total calcium, phosphorus, cholesterol, triglycerides, random glucose, sodium, chloride, potassium |
| Urinalysis | Dipstick with subsequent microscopic evaluation if positive for blood |

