## Laboratory assessments

Laboratory assessments post-screening are noted in Table 3 and will be carried out as per the schedules in Table 1.

Table 3 Laboratory Assessments

| Hematology | Complete blood count (hemoglobin, hematocrit, total white blood cell [WBC] count, differential WBC count [neutrophils, lymphocytes, monocytes, eosinophils, basophils]), platelet count, international normalized ratio (INR) |
| --- | --- |
| Clinical chemistry | ALT, AST, GGT, total bilirubin, alkaline phosphatase, total protein, albumin, blood urea nitrogen (BUN)/urea, creatininee, uric acid, total calcium, phosphorus, cholesterol, triglycerides, random glucose, sodium, chloride, potassium |
| Urinalysis | Dipstick with subsequent microscopic evaluation if positive for blood |
| Immunology and special chemistry | Alfa-fetoprotein, ANA |
| HBV serology and virology | HBeAg, anti-HBe, HBsAg, anti-HBs, quantitative HBsAg and  HBeAg, HBV-DNA |
| Thyroid function tests | FT3, FT4, TSH |
| HCG pregnancy test | For females of childbearing potential, subjects will have pregnancy tests performed as per the schedules in Table 1. |

HBsAg will be assessed by the central laboratory. Other parameters will be assessed by a local laboratory, normal ranges for the local laboratory parameters must be supplied to designee before the study starts and at any point that the normal ranges are changed.

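### The albumin line of the decompensation exclusion is printed tenfold too low and has no effect; secondarily, the creatinine entry and stopping limits can overlap at some local laboratories

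*Protocol*

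**What the plan says.** **Albumin.** Section 6.4 (Exclusion Criteria) excludes decompensated liver disease, given as a Child-Pugh score above 5. It then says what that means in practice: "if one of the following 5 conditions are met, the patient must be excluded". The first condition is "Serum albumin <3.5 g/L". Prothrombin time, bilirubin, encephalopathy, variceal bleeding and ascites follow. Further down the same list, haemoglobin is in different units: "Hemoglobin <11.5 g/dL for females and <12.5 g/dL for men".

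Other parts of the protocol bear on the same patients:
- The synopsis excludes decompensated disease "defined as a Child-Pugh Score B or C".
- Section 6.3 requires "Absence of cirrhosis determined by liver ultrasound".
- Table 2 in section 7.2 includes albumin among the screening chemistry tests.

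No other section restates or corrects the albumin limit.

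**Creatinine.** Section 6.4 excludes "Serum creatinine level >1.5 ULN in screening period". On who measures it, section 7.5 says that HBsAg goes to the central laboratory and then: "Other parameters will be assessed by a local laboratory". Section 8.1 (Stopping rules) lists renal failure among the events that stop an individual subject, and includes in it a creatinine above 100 µmol/L. It gives no baseline value and no change from baseline.

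**The concern.** The albumin limit is an operative threshold in a safety screen, and patients who pass that screen may receive up to 96 weeks of Peg-IFN in Arms B and C. As printed it does no work. Section 6.4 makes the list the meaning of the Child-Pugh criterion, so a site that follows the list literally has no albumin cut-off. A site that scores Child-Pugh from the screening albumin may still count a low value. Two sites could therefore apply the same exclusion differently.

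For creatinine, one limit is relative to a local reference range and the other is absolute. If the relative entry ceiling lies above the absolute stopping limit, a patient can be properly enrolled and then meet a stopping rule with no change in renal function. That would be a treatment discontinuation produced by the wording of the plan and not by the drug.

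**Working it through.** **1. Albumin units**

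Input: the limit of 3.5 g/L in section 6.4. Conversion: 1 g/dL = 10 g/L.

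- As printed: 3.5 g/L ÷ 10 = 0.35 g/dL.
- With the number kept and the unit changed to g/dL: 3.5 g/dL × 10 = 35 g/L.
- Ratio: 35 ÷ 3.5 = 10.

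That 3.5 g/dL was meant is an inference. It rests on the haemoglobin line in the same list, which uses g/dL, and on the implausibility of the printed value. That no candidate would fall below 3.5 g/L is clinical common knowledge; the protocol gives no albumin reference range.

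**2. What remains of the decompensation screen**

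Six conditions are listed: albumin, prothrombin time, bilirubin, encephalopathy, variceal bleeding and ascites. One is inactive and 6 − 1 = 5 still work. The lead-in announces five conditions, but since any one of them excludes, the miscount changes no decision.

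**3. Creatinine: when do the limits overlap?**

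Inputs: entry ceiling 1.5 × ULN (section 6.4); stopping limit 100 µmol/L (section 8.1). The ULN is not in the protocol. I take it to be the local laboratory's at screening as well as later, although the sentence in section 7.5 stands among the post-screening tests.

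Overlap requires 1.5 × ULN > 100, that is, ULN > 100 ÷ 1.5 = 66.7 µmol/L.

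The ULN values below are assumptions, chosen to show the range:

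| Assumed ULN (µmol/L) | Entry ceiling, 1.5 × ULN | Width of overlap above 100 | Stopping limit as a multiple of ULN (100 ÷ ULN) |
|---|---|---|---|
| 60 | 90 | none | 1.67 |
| 70 | 105 | 5 | 1.43 |
| 80 | 120 | 20 | 1.25 |
| 90 | 135 | 35 | 1.11 |
| 100 | 150 | 50 | 1.00 |
| 110 | 165 | 65 | 0.91 |

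At an assumed ULN above 100 µmol/L, the stopping limit falls inside the laboratory's own normal range.

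**4. When could the stopping rule first bite?**

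Table 1 marks biochemistry, which includes creatinine, at all 29 visits. Section 7.4 places all baseline assessments before the first dose, so the Day 0 result comes before there is any study treatment to stop. The first visit on treatment is Week 2.

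**The case against.** **On albumin.** A serum albumin of 3.5 g/L is so implausible that a site would probably recognise the slip. The Child-Pugh score stands in the same criterion, and albumin is measured at screening. Many of the patients the line would catch are screened out elsewhere: by the no-cirrhosis requirement, by ultrasound and elastography, and by the other five conditions. The investigator may also refuse anyone judged unsuitable, and hepatic decompensation is itself a stopping event.

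Most of this stands, and it makes the practical reach small. It does not make the line correct. Ultrasound does not measure albumin, the synopsis defines decompensation by Child-Pugh class and not by a score above 5, and investigator discretion is not a limit. A reader might infer that the whole decompensation exclusion is void. The protocol does not support that, because only the albumin line fails.

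**On creatinine.** Mixing a relative entry limit with an absolute stopping limit is not an error in itself. The stopping item is headed as renal failure and sits among events, so it can be read as a new occurrence on treatment and not as a stable pre-treatment value. The overlap also needs a ULN that the protocol does not give.

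These objections largely stand, and they are why the point is secondary. They do not remove it: the item's wording lets the number act as a trigger by itself, with no baseline qualifier. A reader might go further and infer that a patient could have to stop at Day 0. Section 7.4 rules that out, because baseline assessments precede the first dose.

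**Conclusion.** **Albumin: wrong as written, high confidence.** The printed limit is tenfold too low and one of six listed conditions has no effect. The correction to 35 g/L assumes that the number is right and the unit is wrong. The number of patients affected is unknown and probably small, given the other cover.

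**Creatinine: a conditional inconsistency, lower confidence.** The limits overlap only where the local ULN exceeds 66.7 µmol/L and the stopping item is read literally. On those assumptions, an eligible patient may meet the stopping rule from Week 2 with unchanged renal function. The table's overlap widths illustrate assumed ULNs and are not findings about the six centres. A reader might infer that the two limits necessarily contradict each other. They do not: at a ULN of 60 µmol/L there is no overlap.

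Neither point touches sample size, power or alpha. Both concern eligibility and safety, and both should be corrected.

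**What to change.** 1. In section 6.4, change the albumin line to <35 g/L (3.5 g/dL). Correct the announced count from five to six in the same edit, as an incidental wording change.
2. State the creatinine entry and stopping limits on one scale, either both in µmol/L or both as multiples of ULN, with the entry limit no higher than the stopping limit. The sponsor's clinicians should choose the value.

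The cost is amendment wording. Albumin and creatinine are already among the screening tests in Table 2, so no test is added. There may be a few more screen failures once the albumin line works, or if the creatinine entry limit is lowered.

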# Schedule of assessments and procedure

## Schedule of assessments

Table 1 Schedule of assessments

| Flowchart | Screening | Treatment period | | | | | | | | | | | | | | | | | | | | | | | | | | Follow-up | |
| --- | --- | --- | --- | --- | --- | --- | --- | --- | --- | --- | --- | --- | --- | --- | --- | --- | --- | --- | --- | --- | --- | --- | --- | --- | --- | --- | --- | --- | --- |
| Visit | V1 | V2 | V3 | V4 | V5 | V6 | V7 | V8 | V9 | V1  0 | V1  1 | V1  2 | V1  3 | V1  4 | V1  5 | V1  6 | V1  7 | V1  8 | V1  9 | V2  0 | V2  1 | V2  2 | V2  3 | V2  4 | V2  5 | V2  6 | V2  7 | V28 | V29 |
| Study  Weeks  (w) | -8w-0d | 0d | 2w  ±  3d | 4w  ±  3d | 8w  ±  3d | 12 w  ±  3d | 16 w  ±  3d | 20 w  ±  3d | 24 w  ±  3d | 28 w  ±  3d | 32 w  ±  3d | 36 w  ±  3d | 40 w  ±  3d | 44 w  ±  3d | 48 w  ±  3d | 52 w  ±  3d | 56 w  ±  3d | 60 w  ±  3d | 64 w  ±  3d | 68 w  ±  3d | 72 w  ±  3d | 76 w  ±  3d | 80 w  ±  3d | 84 w  ±  3d | 88 w  ±  3d | 92 w  ±  3d | 96 w  ±  3d | 108 w  ±  7d | 120 w  ±  7d |
| Written informed  consent | X |  |  |  |  |  |  |  |  |  |  |  |  |  |  |  |  |  |  |  |  |  |  |  |  |  |  |  |  |
| Collect medical  history | X |  |  |  |  |  |  |  |  |  |  |  |  |  |  |  |  |  |  |  |  |  |  |  |  |  |  |  |  |
| Physical  examination | X | X | X | X | X | X | X | X | X | X | X | X | X | X | X | X | X | X | X | X | X | X | X | X | X | X | X | X | X |
| Signs and symptoms | X | X | X | X | X | X | X | X | X | X | X | X | X | X | X | X | X | X | X | X | X | X | X | X | X | X | X | X | X |
| Blood  coagulation | X |  |  |  |  |  |  |  | X |  |  |  |  |  | X |  |  |  |  |  | X |  |  |  |  |  | X |  | X |
| HCG^1^ |  | X |  |  |  |  |  |  |  |  |  |  |  |  | X |  |  |  |  |  |  |  |  |  |  |  | X |  |  |
| Routine urine  test^2^ | X | X |  |  |  |  |  |  | X |  |  |  |  |  | X |  |  |  |  |  | X |  |  |  |  |  | X |  |  |
| Abdominal  ultrasound | X |  |  |  |  |  |  |  | X |  |  |  |  |  | X |  |  |  |  |  | X |  |  |  |  |  | X |  |  |
| ECG | X |  |  |  |  |  |  |  |  |  |  |  |  |  | X |  |  |  |  |  |  |  |  |  |  |  | X |  |  |
| Chest X ray | X |  |  |  |  |  |  |  |  |  |  |  |  |  | X |  |  |  |  |  |  |  |  |  |  |  | X |  |  |
| Ophthalmo-  logical  examination | X |  |  |  |  | X |  |  | X |  |  |  |  |  | X |  |  |  |  |  | X |  |  |  |  |  | X |  |  |
| AFP | X |  |  |  |  |  |  |  |  |  |  |  |  |  | X |  |  |  |  |  |  |  |  |  |  |  | X |  | X |
| Routine  Blood  test^3^ | X | X | X | X | X | X | X | X | X | X | X | X | X | X | X | X | X | X | X | X | X | X | X | X | X | X | X | X | X |
| biochemical indexes^4^ | X | X | X | X | X | X | X | X | X | X | X | X | X | X | X | X | X | X | X | X | X | X | X | X | X | X | X | X | X |
| HBeAg^5^ | X | X |  |  |  | X |  |  | X |  |  | X |  |  | X |  |  | X |  |  | X |  |  | X |  |  | X |  | X |
| HBsAg^5^ | X | X |  |  |  | X |  |  | X |  |  | X |  |  | X |  |  | X |  |  | X |  |  | X |  |  | X |  | X |
| HBsAb^5^ |  |  |  |  |  |  |  |  | X |  |  |  |  |  | X |  |  |  |  |  | X |  |  |  |  |  | X |  | X |
| HBV DNA^5^ | X | X |  |  |  | X |  |  | X |  |  | X |  |  | X |  |  | X |  |  | X |  |  | X |  |  | X | X |  |
| T3，T4，TSH | X |  |  |  |  | X |  |  | X |  |  | X |  |  | X |  |  | X |  |  | X |  |  | X |  |  | X |  | X |
| Fibroscan | X |  |  |  |  |  |  |  | X |  |  |  |  |  | X |  |  |  |  |  | X |  |  |  |  |  | X |  | X |
| ANA | X |  |  |  |  |  |  |  |  |  |  |  |  |  | X |  |  |  |  |  |  |  |  |  |  |  | X |  | X |
| HIV, HAV,  HCV, HDV,  HEV | X |  |  |  |  |  |  |  |  |  |  |  |  |  |  |  |  |  |  |  |  |  |  |  |  |  |  |  |  |
| Adverse events |  | X | X | X | X | X | X | X | X | X | X | X | X | X | X | X | X | X | X | X | X | X | X | X | X | X | X | X | X |
| Medication dispensed |  | X | X | X | X | X | X | X | X | X | X | X | X | X | X | X | X | X | X | X | X | X | X | X | X | X |  |  |  |
| Medication  returned |  |  | X | X | X | X | X | X | X | X | X | X | X | X | X | X | X | X | X | X | X | X | X | X | X | X | X |  |  |
| Serum sample | X | X |  | X |  | X |  |  | X |  |  | X |  |  | X |  |  | X |  |  | X |  |  | X |  |  | X | X | X |
| Whole  blood  sample | X | X |  | X |  | X |  |  | X |  |  | X |  |  | X |  |  | X |  |  | X |  |  | X |  |  | X | X | X |
| Immunologic parameters^6^ | X | X |  | X |  | X |  |  | X |  |  | X |  |  | X |  |  |  |  |  | X |  |  |  |  |  | X | X |  |
| PBMC^6^ | X | X |  | X |  | X |  |  | X |  |  | X |  |  | X |  |  | X |  |  | X |  |  | X |  |  | X | X | X |
| Liver biopsy |  | X |  |  |  |  |  |  |  |  |  |  |  |  | X |  |  |  |  |  |  |  |  |  |  |  |  |  | X |

^1^HCG testing: Only performed in female patients within 24 hours of the first dose of study drug;

1. Routine urine test includes pH value, red blood cell, white blood cell, urine sugar and proteinuria;
2. Routine blood test includeS hemoglobin, red blood cell counts, white blood cell counts, neutrophils, lymphocytes, monocytes, and platelet counts;
3. Blood biochemical indexes include ALT, AST, total bilirubin, total cholesterol, triglycerides, total protein, albumin, urea nitrogen, creatinine, serum potassium, calcium, phosphorus, blood glucose;
4. Quantitative HBsAg will be performed by central lab;
5. Immunologic parameters study and PBMC separation & freezing only performed in center of Tongji hospital.

